## Abstract

**Background:**

Motor imagery ability (MIA) is a critical cognitive process that enables the mental simulation of movements, facilitating skill acquisition in the use of myoelectric prostheses and their effective control in individuals who have undergone amputation. Although MIA is essential, its impact on upper extremity function and proprioception in myoelectric prosthesis users remains insufficiently studied.

**Objective:**

This study aims to evaluate MIA in individuals who have undergone transradial amputation and use myoelectric prostheses, compare it with a healthy control group, and examine its association with upper extremity functionality and proprioception.

**Methods:**

This cross-sectional study will include 15 individuals who have undergone transradial amputation (aged 18-65 y) and 15 age- and sex-matched healthy controls, recruited from prosthetics and orthotics centers in Istanbul, Turkey. Assessments will include MIA, hand mental rotation, upper extremity function, and proprioception. MIA will be measured using the Movement Imagery Questionnaire-3 and the Mental Chronometry Test. Hand mental rotation ability will be assessed via the Orientate mobile app. Upper extremity function will be evaluated using the Box and Block Test; Jebsen-Taylor Hand Function Test; and the Quick Disabilities of the Arm, Shoulder, and Hand questionnaire. Proprioception will be assessed through joint position sense measurements. All data will undergo appropriate statistical analyses.

**Results:**

Data collection began following funding from the Scientific and Technological Research Council of Turkey on April 25, 2025. As of November 2025, 8 participants with transradial amputation and 8 healthy controls have been recruited. Assessments are ongoing, and study completion is expected by June 2026.

**Conclusions:**

This study will evaluate MIA in individuals who have undergone transradial amputation and use myoelectric prostheses and explore its relationship with upper extremity function and proprioception. The findings are expected to guide the development of targeted rehabilitation strategies, particularly those incorporating motor imagery–based training for this population.

**International Registered Report Identifier (IRRID):**

DERR1-10.2196/83787

## Introduction

Amputation refers to the surgical removal of a limb along with its associated anatomical structures and is commonly performed due to trauma, infection, vascular diseases, or malignancies [1,2]. Among upper limb amputations, transradial amputations are the most common, accounting for more than 30% of the cases [3,4]. The anatomical complexity and functional importance of the forearm make transradial amputations particularly significant in both preoperative evaluation and postoperative management [5,6].

Following upper limb amputation, significant morphological and neurophysiological changes occur [7]. The loss of sensory input and visual feedback leads to neuroplastic remodeling within the central nervous system, resulting in extensive reorganization of cortical representation areas, particularly within the motor and somatosensory cortices [8,9]. These cortical topography alterations involve the reshaping of representational maps related to the missing limb and reflect both functional and structural adaptations [10,11]. Recent studies have highlighted that neuroplastic changes are especially pronounced in the somatosensory, premotor, and parietal cortices, which appear to form new neural connections despite the absence of peripheral sensory input following amputation [11,12]. Such neuroplastic adaptations are thought to play a crucial role in prosthesis use and motor learning.

Motor imagery (MI) is defined as the mental simulation of movement without actual physical execution and has gained considerable attention in neurodevelopment and rehabilitation research. During MI, brain regions involved in movement—such as the motor, premotor, and somatosensory cortices—are activated, highlighting their important role in motor planning and learning processes [13,14]. MI is typically classified into 2 main types: visual and kinesthetic imagery. Visual imagery involves mentally observing a movement from an external viewpoint, while kinesthetic imagery encompasses the internal experience of muscular activity and proprioceptive sensations [15]. Following amputation, neuroplastic changes in the somatosensory cortex may impair MI ability (MIA), reducing the capacity to mentally simulate movements [11]. Assessing MIA in individuals with limb loss is essential for understanding the clinical consequences of such neuroplastic alterations and tailoring personalized rehabilitation strategies. Deficits in MI can directly affect prosthetic adaptation and compromise the success of motor rehabilitation [16,17].

Myoelectric prosthetic systems function by detecting biopotential signals generated by residual muscle activity; however, effective prosthetic control relies not only on muscle contractions but also on cognitive processes, such as MI. Specifically, kinesthetic MI supports prosthetic control at the mental level, playing a key role in learning and adaptation. These cognitive processes are believed to promote neuroplasticity by enhancing the interaction between the central nervous system and muscular structures, thereby facilitating more efficient prosthesis control [18,19]. MI enables mental control of the prosthesis without direct muscle activation and improves cortical efficiency during prosthetic use. Consequently, both MI and proprioceptive awareness are fundamental for functional performance and neural adaptation in myoelectric prosthesis users [19].

In individuals who have undergone upper limb amputation, the preservation of MIA may significantly influence the process of adapting to myoelectric prostheses. Previous studies have demonstrated that individuals with higher MIA tend to perform functional tasks more effectively when using a prosthesis [20,21]. In this context, MI can be considered a potential facilitator for enhancing the functionality of myoelectric prostheses and improving upper limb performance. Furthermore, MI-based rehabilitation protocols have been shown to support neuroplasticity by strengthening the interaction between the central nervous system and prosthetic control mechanisms [19]. These findings underscore the clinical importance of assessing and enhancing MIA in myoelectric prosthesis users.

Proprioceptive feedback is a fundamental component in the perception and control of movement, as it transmits sensory information from muscles, tendons, and joints to the central nervous system [22]. Following amputation, the reduction or loss of these sensory inputs may impair MI processes, given that MI involves the mental simulation of both kinesthetic and somatosensory information [10,23]. Recent studies have shown that diminished proprioceptive input is associated with decreased MIA, which may lead to reduced performance in prosthetic control [24-26]. Therefore, preserving or restoring proprioceptive functions is crucial to supporting MI capacity in individuals with limb loss and, consequently, enhancing prosthesis use.

The physiological, psychological, and particularly cortical changes that occur following amputation require a multidimensional approach to managing individuals with limb loss. In this context, assessing MIA in people with transradial amputation has become increasingly important, as it contributes to the reorganization of motor control and supports cortical representation. Specifically, in the context of myoelectric prosthesis use, MI plays a complementary role by enhancing functional integration with the prosthesis and facilitating both movement planning and execution. This study aims to evaluate the MIAs of individuals with transradial amputation who use myoelectric prostheses by comparing them with healthy controls and investigate the impact of MI on functionality and proprioception. The findings are expected to provide a scientific foundation for integrating MI-based approaches into prosthetic rehabilitation programs.

## Methods

### Participants

The required sample size for the study was determined using G*Power software (version 3.1; Heinrich Heine University Düsseldorf). The calculation was based on the Movement Imagery Questionnaire-3 (MIQ-3) scores reported by Saimpont et al [27], which served as a reference for the primary outcome of this study.

Although Saimpont et al [27] reported a large effect size (Cohen *d*=1.41) in a healthy population, a more conservative estimate (Cohen *d*=0.8) was applied in this study’s power analysis to better reflect expected variability among participants who underwent transradial amputation. Using a 2-tailed independent samples *t* test, with an α of .05 and power (1–β) of .80, the required total sample size was calculated as 30 participants (n=15, 50% per group).

This sample size provides sufficient statistical power to detect large effects (Cohen *d*≥0.8) between groups while also allowing for potential participant dropouts. A sensitivity analysis showed that detecting moderate effects (Cohen *d*=0.6) would require approximately 18 participants to achieve equivalent power; however, as the study primarily aims to detect large between-group differences, the planned sample of 30 participants (n=15, 50% per group) was considered adequate.

Participants will be recruited from prosthetics and orthotics centers located in Istanbul, Turkey. The study group will consist of volunteers who meet the inclusion criteria; therefore, no probabilistic sampling method will be used. Inclusion criteria for the amputee and control groups are listed in Textbox 1.

Inclusion criteria for the amputee and control groups.

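### Fifteen per group gives about 56% power for d=0.8, not 80%, and the figure of 18 participants for d=0.6 is wrong on any reading

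*Protocol article*

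**What the plan says.** Everything is in one place, the Participants section of the Methods.

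- **Test and error rates:** "Using a 2-tailed independent samples *t* test, with an α of .05 and power (1–β) of .80".
- **Effect size:** the reference study "reported a large effect size (Cohen *d*=1.41) in a healthy population"; for this study "a more conservative estimate (Cohen *d*=0.8) was applied in this study’s power analysis".
- **Result:** "the required total sample size was calculated as 30 participants (n=15, 50% per group").
- **Claims built on it:** the section calls this enough to detect d of 0.8 or more, "while also allowing for potential participant dropouts".
- **Sensitivity statement:** "detecting moderate effects (Cohen *d*=0.6) would require approximately 18 participants to achieve equivalent power". It does not say whether 18 is a total or a per-group number.

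The Study Design section repeats 15 per group. Outcome Measures names the MIQ-3 as the primary outcome, so this is the power statement for the primary comparison.

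**The concern.** Two things stand out before any calculation. First, 15 per group is well below what an independent-samples t test usually needs for d=0.8 at 80% power. Second, the section gives 30 participants for d=0.8 and then 18 for the smaller d=0.6 at the same power. If both are totals, the order is reversed, since a smaller effect always needs more participants.

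What is at stake is how the primary result will be read. If readers believe that a difference of 0.8 SD would be found four times in five, they will take a non-significant MIQ-3 comparison as fair evidence that imagery ability is preserved after amputation. The Discussion (Expected Outcomes) reports earlier work in which prosthesis users performed like healthy people on hand mental rotation, so a reader could easily make that step. If the true power is little better than a coin toss, the step is not justified.

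**Working it through.** **Inputs**, all from the Participants section: two-sided independent-samples t test, alpha .05, target power .80, 1:1 allocation, d=0.8 (main) and d=0.6 (sensitivity). Because d is standardized, no SD or outside figure is needed.

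**Formula.** With n per group, df = 2n − 2 and noncentrality λ = d·√(n/2). Power = P(|T| > t(.975, df)), where T is noncentral t with df and λ. This is the exact method for the stated test.

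**1. Attempt to reproduce 15 per group at d=0.8**

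- λ = 0.8·√7.5 = 2.191; df = 28; critical t = 2.048. Power = **0.562**, against .80 stated.
- n = 25: λ = 0.8·√12.5 = 2.828; df = 48; critical t = 2.011. Power = 0.791, too low.
- n = 26: λ = 0.8·√13 = 2.884; df = 50; critical t = 2.009. Power = 0.807, enough.

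The unrounded solution is 25.5, so **26 per group, 52 in total**. A normal approximation gives 25 per group, so the choice of method does not explain 15.

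**2. The d=0.6 statement**

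| n per group | λ = 0.6·√(n/2) | Power |
|---|---|---|
| 9 (18 as a total) | 1.273 | 0.224 |
| 15 (planned) | 1.643 | 0.355 |
| 18 (18 per group) | 1.800 | 0.417 |
| 44 | 2.814 | 0.795 |
| 45 | 2.846 | 0.804 |

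The requirement is **45 per group, 90 in total**.

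**3. What 15 per group can do**

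- Smallest effect with 80% power: d = 1.06 (λ = 1.06·√7.5 = 2.903; power 0.800).
- Half-width of the 95% confidence interval for the group difference, in SD units: t(.975, 28)·√(2/15) = 2.048 × 0.365 = 0.75.

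**4. The dropout claim**

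The sample is 52 − 30 = 22 short before any loss. At d=0.8, power is 0.531 with 14 per group and 0.499 with 13 per group.

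**5. Alternative readings tried**

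- *One-sided test at .05:* needs 21 per group; 15 per group gives 0.689. It would also contradict the text, which states two-tailed testing.
- *Paired t test with dz=0.8:* needs 14.3, so 15 pairs (power 0.821). This matches the 15, but the section names an independent-samples test, and a between-group d of 0.8 equals dz=0.8 only if the within-pair correlation is 0.5, because dz = d/√(2(1−ρ)). No such correlation is assumed.
- *Independent t test with d=1.41:* needs 8.97, so 9 per group, 18 in total. This matches the 18, but it is attached to d=0.6.

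The last two matches suggest where the printed numbers may have come from. That is inference only, and nothing below depends on it.

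**The case against.** The arithmetic for the stated test is not open to dispute. The best case on the other side concerns what surrounds it.

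- **The 18 may be per group.** The next clause defends the planned sample on the ground that large effects are the target, which makes most sense if 18 is more than is planned, that is, 18 per group against 15. On that reading the section does not contradict itself. This is fair, but the figure remains wrong: 18 per group gives 42% power, and 45 are needed.
- **The planned analysis is ANCOVA, not a t test.** Textbox 2 adjusts the imagery comparisons for covariates, which can raise power. Assuming three covariates unrelated to group (25 error df), power at d=0.8 is about 56% if they explain none of the outcome variance, 65% if they explain 20%, and close to 80% only at about 43%. So 56% belongs strictly to the stated t test. But the protocol assumes no explained variance, so ANCOVA does not support the 80% claim.
- **The design is adequate for very large effects.** At d=1.41, 15 per group gives 96% power. True, but the protocol itself set that value aside as too optimistic.
- **Dropout may be small.** Each participant is assessed once, so the 14 and 13 per group are illustrations. Even with no loss, the claimed reserve does not exist.
- **No passage says that a null result will be read as preserved ability.** Correct. The Discussion speaks of similarities and differences, and the Introduction expects possible impairment. The misreading is a risk, not a stated plan. Strengths and Limitations mentions sample size only in relation to generalizability, so nothing there guards against it.

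**Conclusion.** The point holds, and the section must be corrected. On the protocol's own inputs, the required size for d=0.8 is 52, not 30. The planned 30 gives 56% power, so the stated test would miss a true difference of 0.8 SD about 44% of the time. The detectable effect at 80% power is d=1.06. The figure of 18 for d=0.6 is wrong as a total (22% power) and as a per-group number (42% power); 90 in total are needed. The claim of sufficient power for d of 0.8 or more and the claim of a dropout allowance both fall with the main figure.

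This rests on the stated test, equal groups and the usual t-test assumptions. Only covariates explaining about 43% of MIQ-3 variance, or a matched-pairs analysis with a within-pair correlation of about 0.5, would bring 15 per group near 80% power at d=0.8. The protocol assumes neither.

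**What to change.** Keep 15 per group if recruitment cannot be extended, and replace the power statement with wording such as:

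> Fifteen participants per group give 80% power for d of 1.06 or more and 56% power for d=0.8 (two-sided independent-samples t test, alpha .05). Detecting d=0.8 with 80% power would need 26 per group, and d=0.6 would need 45 per group. No allowance is made for missing data.

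Delete the 18-participant sentence, the claim of sufficient power for d of 0.8 or more, and the dropout claim. Add that the primary result will be read from the group difference and its 95% confidence interval, and that a non-significant difference will not be taken as evidence of preserved imagery ability. This last addition is advice on interpretation; the numerical corrections are needed with or without it.

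The cost is a wording change and a less favourable power figure. No extra participants or change in procedure are needed. The timing is good: the Results section reports 16 of 30 recruited by November 2025 and no statistical analyses yet, so the correction can be made before any result is known.

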### Ethical Considerations

This study was approved by the noninterventional clinical research ethics committee of Istanbul Medipol University (E-10840098-202.3.02-2988) on May 9, 2024. All procedures will be conducted in accordance with the principles outlined in the Declaration of Helsinki. Before participation, all individuals will be informed about the study through both written and verbal explanations. Those who agree to take part will be asked to sign an informed consent form. The form explicitly states that participation is entirely voluntary and free of charge and that participants may withdraw from the study at any time without providing a reason or facing any consequences.

No additional costs will be incurred by the participants, and no compensation will be provided. All personal and identifying data will be kept strictly confidential. The collected data will be used solely for scientific purposes and without any commercial intent. Where necessary, anonymized data may be subjected to statistical analysis without the need for further ethics approval, provided that such use is covered by the initial consent.

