### Study Design

This study is registered in the ClinicalTrials.gov database (NCT06541379) and uses a cross-sectional design with multicenter recruitment and single-center assessment. Participants will be recruited from several prosthetics and orthotics clinics located in Istanbul, Turkey, while all evaluations will be conducted at the prosthetics and orthotics research and application center of Istanbul Medipol University. All necessary institutional approvals were obtained before study initiation.

A total of 30 participants will be included: 15 (50%) individuals with unilateral transradial amputation who use a myoelectric prosthesis and 15 (50%) healthy control participants matched for age and sex. The study flowchart describing the recruitment and assessment process is presented in Figure 1.

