**Missing data, outliers, and multiple comparisons**
Missing data will undergo listwise deletion.Trials with outlier values exceeding 2 SDs from the group mean will be excluded. Sensitivity analyses with and without outliers will be performed.The Bonferroni correction will be applied for multiple comparisons.

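### The sample of 30 is said to allow for dropouts, but 30 is also the calculated requirement, so the allowance is zero; the practical effect is small

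*Protocol article*

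**What the plan says.** All the sizing statements are in the protocol article.

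- **Participants, requirement:** from a two-sided independent-samples t test at d=0.8, alpha .05 and power .80, "the required total sample size was calculated as 30 participants (n=15, 50% per group").
- **Participants, claim:** the next paragraph says that this size has sufficient power for large effects "while also allowing for potential participant dropouts". It ends by naming 30, again 15 per group, as the planned sample.
- **Study Design:** "A total of 30 participants will be included", with 15 planned in each group.
- **Ethical Considerations:** "participants may withdraw from the study at any time without providing a reason or facing any consequences".
- **Textbox 2, missing data:** "Missing data will undergo listwise deletion".

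The article gives no dropout rate, inflated number or replacement rule. Outcome Measures says that each participant is assessed once. The JPS section puts the MIQ-3 first in a session of about 90 minutes. Results reports 16 people recruited by November 2025, 8 per group, with all their assessments completed and no statistical analysis yet done.

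**The concern.** An attrition allowance is the difference between the number to be enrolled and the number that the calculation says must be analysed. Here one figure serves as both, so the article claims a protection that its own numbers do not contain. The point is not that a dropout rate has been left out, which an article may leave to a fuller protocol. It is that the article makes a positive statement and its own figures contradict it.

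At stake is mainly what readers are told. They will take it that a few losses are covered. In fact a participant who yields no MIQ-3 data and is not replaced leaves the study below the number it says it needs.

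**Working it through.** **Inputs (Participants section).** The test: "Using a 2-tailed independent samples *t* test". The error rates: "with an α of .05 and power (1–β) of .80". The effect: "a more conservative estimate (Cohen *d*=0.8) was applied in this study’s power analysis". Required and planned totals: 30 and 30.

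**Step 1: the margin.** Planned − required = 30 − 30 = 0, or 15 − 15 = 0 per group. For comparison, an allowance on top of 15 per group, n/(1 − rate), would be 15/0.95 = 15.8, so 16 per group (32 in total) at an assumed 5% loss. At an assumed 10% it would be 15/0.90 = 16.7, so 17 per group (34 in total). The article gives no rate.

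**Step 2: could 30 already include slack?** It would have to be an inflated version of a smaller requirement. For the stated t test, power comes from the noncentral t distribution with 2n − 2 degrees of freedom and noncentrality d√(n/2).

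| n per group | Noncentrality at d=0.8 | Power |
|---|---|---|
| 15 | 0.8 × √7.5 = 2.19 | 0.562 |
| 25 | 0.8 × √12.5 = 2.83 | 0.791 |
| 26 | 0.8 × √13 = 2.88 | 0.807 |

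The solution for 80% power is 25.5, so 26 per group (52 in total). The article's 30 is not reproduced. A normal approximation gives 25 per group, and a one-sided test gives 20 to 21. A paired test with a standardised difference of 0.8 does give 15 (14.3 pairs, rounded up), but that is not the stated test, and 15 would still be the requirement with nothing added. With 15 per group, the effect detectable at 80% power is about d=1.06. No slack is hidden.

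**Step 3: how likely is a loss?** At the November 2025 report, 30 − 16 = 14 participants remained to be enrolled. I assume independent losses at a common rate among those 14 and none among the 16 already assessed.

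| Assumed loss rate | Expected losses | Chance of at least one |
|---|---|---|
| 5% | 14 × 0.05 = 0.7 | 1 − 0.95^14 = 0.51 |
| 10% | 14 × 0.10 = 1.4 | 1 − 0.90^14 = 0.77 |

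These are chances of a loss occurring. The study finishes short only if the loss is not made up.

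**Step 4: what does a loss cost?** Power at d=0.8, two-sided .05:

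| Analysed | Power |
|---|---|
| 15 v 15 | 0.562 |
| 15 v 14 | 0.546 |
| 14 v 14 | 0.531 |
| 13 v 13 | 0.499 |

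One loss costs about 0.016. The fall to 0.50 takes four losses, well above the 0.7 to 1.4 expected.

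**The case against.** The strongest reply is that the study is barely exposed to dropout. There is no follow-up to lose, the primary outcome is collected first, and more than half the sample had completed all assessments. This stands, and it is why the effect is rated small. It does not make the clause true.

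A reader might infer more than the documents support in four ways:

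- **Every withdrawal takes the study below target.** This would need recruitment to stop at 15 per group with no replacement. The article fixes the number to be included but states no such rule. It describes consecutive recruitment of eligible people during the recruitment period, so a lost participant could be replaced.
- **The chance of falling short is 79% or 96%.** These figures are 1 − 0.95^30 and 1 − 0.90^30. They treat all 30 as still to be assessed, although 16 already have been.
- **Any session stopped early loses a participant.** Someone who stops after the MIQ-3 has given primary data. The listwise-deletion sentence does not say that a missing later test removes a person from the MIQ-3 comparison.
- **A loss breaks a matched pair.** The controls are matched on age and sex, but the article does not say individually, and the stated t test and analysis of covariance are unpaired.

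It may also be said that the low power belongs to the base calculation and not to dropout. That is right: the drop from 0.80 to 0.56 is a separate error. But correcting the base number and leaving the dropout clause would keep the unsupported claim, and deleting the clause would not correct the base number.

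**Conclusion.** The statement that 30 participants also cover dropouts is wrong on the article's own figures: the allowance is 0 of 30, and the stated inputs give no hidden reserve. This needs no assumption about loss rates.

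The practical consequence is small. Under assumed loss rates of 5% to 10% among the 14 still to be enrolled, the chance of at least one loss is 51% to 77%, and one unreplaced loss lowers power at d=0.8 from 0.56 to 0.55. Those figures rest on rates that the documents do not supply. They also assume that the 16 completed assessments remain usable, with no later withdrawal of consent. It is a correction worth making because it is cheap and removes a false assurance, not because attrition threatens the study.

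**What to change.** In the Participants section, delete the dropout clause and state that the sample size contains no attrition allowance. Define the target as 15 participants per group with analysable MIQ-3 data. Anyone without such data is replaced by the next eligible person, keeping the groups matched for age and sex. Where consent for use remains, MIQ-3 data from a participant who stops later in the session stay in the primary analysis, and that person is not replaced.

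Restate the base calculation in the same edit: with 15 per group, power at d=0.8 is about 56%, and the effect detectable at 80% power is about d=1.06. Replacement keeps the groups at 15; it does not bring the stated 80% power. If the base number is raised, the same counting and replacement rule applies to the new target.

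The dropout part costs a few sentences and perhaps one or two extra visits, and does not itself raise the target. With 14 participants still to be enrolled at the last report and no analysis begun, it can be settled before the data are analysed.
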